## Abstract

**Background:**

The nutritional status and health of mothers influence the growth and development of infants during pregnancy and postnatal life. Interventions that focus on improving the nutritional status and lifestyle of mothers have the potential to optimise the development of the fetus as well as improve the health of mothers themselves. Improving the diets of women of childbearing age is likely to require complex interventions that are delivered in a socially and culturally appropriate context. In this study we aim to test the efficacy of two interventions: behaviour change (Healthy Conversation Skills) and vitamin D supplementation, and to explore the efficacy of an intervention that combines both, in improving the diet quality and nutritional status of pregnant women.

**Methods/design:**

Women attending the maternity hospital in Southampton are recruited at between 8 and 12 weeks gestation. They are randomised to one of four groups following a factorial design: Healthy Conversation Skills support plus vitamin D supplementation (1000 IU cholecalciferol) (*n* = 150); Healthy Conversation Skills support plus placebo (*n* = 150); usual care plus vitamin D supplementation (*n* = 150); usual care plus placebo (*n* = 150). Questionnaire data include parity, sunlight exposure, diet assessment allowing assessment of diet quality, cigarette and alcohol consumption, well-being, self-efficacy and food involvement. At 19 and 34 weeks maternal anthropometry is assessed and blood samples taken to measure 25(OH) vitamin D. Maternal diet quality and 25(OH) vitamin D are the primary outcomes. Secondary outcomes are women’s level of self-efficacy at 34 weeks, pregnancy weight gain, women’s self-efficacy and breastfeeding status at one month after birth and neonatal bone mineral content, assessed by DXA within the first 14 days after birth.

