### Secondary outcomes

The secondary outcomes are:Women’s level of self-efficacy at 34 weeks, assessed with the General Self-Efficacy scale [24]Pregnancy weight gain assessed by gain in weight between recruitment and 34 weeks gestationMaternal diet quality one month after birthBreastfeeding status one month after birth (yes/no)Neonatal whole body bone mineral content (BMC), lean and fat mass within 2 weeks after birth assessed by dual-energy X-ray absorptiometry (DXA).

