### Early pregnancy

At around 14 weeks gestation women attend the research clinic at Princess Anne Hospital. The timing of this appointment can be later if they are not recruited by 14 weeks. During the appointment, an interviewer-led questionnaire is administered to gather information on parity, baseline demographic features, diet, smoking, alcohol intake, exercise, sunlight exposure, general health, medication, psychological health and wellbeing, self-efficacy and food involvement. Diet is assessed using a 20-item food frequency questionnaire (FFQ) which was developed from a larger FFQ [23]. Data from the FFQ are used to produce a standardised score (with mean 0 and standard deviation 1.0). This score has been named the ‘prudent diet score’. The 20-item FFQ gives closely comparable scores to the full FFQ and can be used in settings where administration of a longer FFQ is not feasible.

For women in the Healthy Conversation Skills intervention group, this appointment also presents an opportunity for the first Healthy Conversation with a trained research nurse. Women are asked about their lifestyle and health behaviours and what they would like to do to ensure they have healthy pregnancies and healthy babies, and to set some goals for achieving this. Details of the conversations and goals are recorded in a Case Report Form and revisited at future appointments.

Women’s height, weight, skinfold thickness (triceps, biceps, subscapular and suprailiac) and grip strength are measured. Venous blood samples are taken and stored with the aim of measuring biomarkers of quality of diet, including beta carotene and vitamin D. With participants’ consent, blood pellets are stored to allow future DNA analysis.

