### One month after birth

Mothers and their babies are visited at home by an intervention or control nurse, depending on their allocation to Healthy Conversation Skills. Questionnaires are administered repeating the questions used at 34 weeks but also asking questions about infant feeding in order to establish whether breastfeeding has been initiated and is maintained. Mothers in the Healthy Conversation Skills intervention group also have a Healthy Conversation with a research nurse during which the mother’s goals for herself and her baby are reviewed. As before, the content of the conversation is recorded. All mothers are asked whether they consent to be contacted in the future if the study receives funding for a follow-up during childhood.

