### Timing of pregnancy

Many women do not know the exact timing of conception. Thus, gestation based on the timing of a woman’s last menstrual period (LMP) and that based on ultrasound scan often differ. Therefore, women coming for their dating scan between 8 and 12 weeks might find they are actually a few weeks earlier or later in their gestation than they thought. All assessments will be performed as closely as possible to the gestational timing outlined in the protocol. Where this is not possible, the following limits will be observed:Women with gestations between 8 and 17 weeks can be included in the trialDating scans take place between 8 and 12 weeksNuchal translucency scans cannot be performed before 11 weeks, and so women with pregnancies of earlier gestation might be asked to return at 11 or 12 weeksEarly pregnancy visits will be performed as closely as possible to that time but will be acceptable until the anomaly scan at 18–21 weeksThe anomaly scan is performed between 18 and 21 weeksThe 34 week scan will be performed between 33 and 36 weeks but, if delayed, can be performed up to delivery

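### Abstract and body disagree on one secondary outcome at one month and on the early sampling visit, and weight gain starts at a point where no weight is described

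*Protocol article*

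**What the plan says.** **Outcomes at one month.** The abstract (Methods/design) lists women's "self-efficacy and breastfeeding status at one month after birth and neonatal bone mineral content", after listing self-efficacy at 34 weeks. In the body, Secondary outcomes gives "level of self-efficacy at 34 weeks, assessed with the General Self-Efficacy scale" and no later self-efficacy outcome. At one month it lists breastfeeding status and maternal diet quality. The One month after birth section says "Questionnaires are administered repeating the questions used at 34 weeks but also asking questions about infant feeding".

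**Sampling visits.** The abstract states: "At 19 and 34 weeks maternal anthropometry is assessed and blood samples taken to measure 25(OH) vitamin D". The body section Early pregnancy says "At around 14 weeks gestation women attend the research clinic at Princess Anne Hospital". At that visit women's "height, weight, skinfold thickness (triceps, biceps, subscapular and suprailiac) and grip strength are measured", and blood is stored for biomarkers that include vitamin D. The section on 18–21 weeks describes scans, a pill count and a second Healthy Conversation. It mentions neither a blood sample nor maternal anthropometry. The Vitamin D supplementation section has the capsules issued at the 14 week visit.

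**Weight gain.** Secondary outcomes defines it from recruitment to 34 weeks. On the early pregnancy visit the body adds "The timing of this appointment can be later if they are not recruited by 14 weeks", and Timing of pregnancy accepts that visit until the anomaly scan at 18–21 weeks. The 34 week scan is allowed from 33 to 36 weeks and, "if delayed, can be performed up to delivery".

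**Analysis.** Statistical analyses plans t tests, with multiple linear regression to adjust for differences found at baseline, and similar analyses for the secondary outcomes.

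**The concern.** An abstract may shorten a list, but here it names an outcome that the body's list does not contain and leaves out one that it does. Both can be reported, because both are collected. The Background says that the group's earlier behaviour change programme protected self-efficacy while no influence on diet was seen, so these two outcomes could well point in different directions. With two lists in print, either outcome could later be presented as the planned one.

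The visit mismatch matters because capsules start at about 14 weeks. A 14 week sample taken before the first capsule can serve as a baseline for 25(OH)D. A 19 week sample would normally be taken on treatment and cannot.

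For weight gain, the definition starts where no weight is described, and the first and last weighings can each move by several weeks. Raw gain then depends partly on how long each woman was observed.

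**Working it through.** No figure in the plan belongs to this point, so the check is mainly a comparison of sections.

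**1. One-month outcomes**
- Abstract: self-efficacy and breastfeeding status.
- Secondary outcomes: diet quality and breastfeeding status.
- Breastfeeding agrees; the other item is swapped.
- Are both collected? The 34 week visit names self-efficacy among its questionnaires, and Primary outcomes requires the food frequency questionnaire at 34 weeks. The 34 week questions are repeated at one month, so both are available then.

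**2. Early sampling visit**
- Abstract: 19 weeks.
- Early pregnancy: about 14 weeks, with weight and blood for vitamin D.
- 18–21 weeks: neither is mentioned.
- The later 25(OH)D sample, at 34 weeks, agrees in abstract and body.

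**3. Start and end of weight gain** (weeks of gestation)
- Recruitment: 8–12 in the abstract and the recruitment section, up to 17 under Inclusion criteria and Timing of pregnancy.
- First weight described: about 14, acceptable until the scan at 18–21.
- Last weight: no weight is listed in the 34 week visit section, but the abstract and the outcome definition both require one. I take it to be measured at the scan visit, at 33–36.
- Interval as defined, recruitment to 34 weeks: 34 − 8 = 26, 34 − 12 = 22, 34 − 17 = 17.
- Nominal interval as measured: 34 − 14 = 20.
- Shortest measured interval: 33 − 21 = 12.
- Longest within the stated windows: 36 − 14 = 22, and longer if the last visit is delayed beyond 36 weeks.

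A woman recruited at 8–12 weeks and weighed at 14 has 14 − 12 = 2 to 14 − 8 = 6 weeks of the defined interval unobserved. For a woman recruited at 14–17 weeks the gap may be close to zero.

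**4. Are the primary comparisons touched?** Primary outcomes fixes both at 34 weeks, and a t test at 34 weeks needs no baseline. The power statement concerns only these outcomes, and it reproduces. With two-sided alpha 0.025 (sidedness is not stated) and a difference of 0.25 SD, n = 2 × (2.2414 + 0.8416)² / 0.25² = 304.2, so 305 per side against 300 stated. Power at 300 per side is Φ(0.25 × √(300/2) − 2.2414) = Φ(0.820) = 79.4% against 80%. Nothing in this point changes those numbers.

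**The case against.** The body gives an itemised secondary outcome list under its own heading, and the abstract differs from it on one item. A reader might infer that the whole outcome set is open. It is not: the primary outcomes and the other secondary outcomes agree. The abstract names bone mineral content without lean and fat mass, but that is ordinary shortening and not a conflict.

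A reader might also infer that a 19 week sample will be used as the 25(OH)D baseline and so adjust away part of the treatment effect. The documents do not support that. Nowhere is the 19 week sample called a baseline, the primary test needs none, and the body collects its baseline information at the early pregnancy visit, when capsules are issued. This risk exists only if the abstract's schedule were followed for a baseline adjustment.

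Silence is also not exclusion. The sections on recruitment and on 18–21 weeks do not say that no weight or blood is taken, and the visit descriptions are not exhaustive, since the 34 week section omits a weight that the outcome needs. The trial summary figure is not available here. An extra 19 week sample cannot be ruled out.

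On weight gain, one might read the spread of intervals as a bias of several kilograms. That would compare two women at opposite extremes, not two arms. Randomisation balances timing in expectation, and the protocol asks for visits as near the planned gestation as possible. Separate nurse teams see the intervention and control women, so scheduling could differ between them, but nothing in the document shows that it does. Adjustment covariates are normally left to the analysis plan.

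These objections remove the stronger readings. They do not remove the swapped outcome, the 19 against 14 week conflict, or the start point with no described weight.

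**Conclusion.** The point holds as an internal inconsistency with limited reach. One secondary outcome at one month differs between abstract and body, and this changes what the trial would report as planned. The early visit for anthropometry and 25(OH)D is 19 weeks in one place and about 14 in the other. Weight gain is defined from recruitment although the first weight described comes later, and the measured interval can range from 12 to 22 weeks or more. That range is the outer limit of the windows, not a typical spread, and it assumes that the last weight is taken at the 34 week scan visit. Its expected effect on the comparison between arms is added noise rather than bias. No size in kilograms or in lost vitamin D effect can be derived from the document. The primary outcomes, their unadjusted tests and the sample size stand.

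**What to change.** - **Outcome list.** Reconcile the abstract with Secondary outcomes into one list, and state whether self-efficacy at one month, diet quality at one month, or both are on it.
- **Sampling visits.** Reconcile the abstract with the Early pregnancy and 18–21 weeks sections. For any baseline adjustment of 25(OH)D, use only the sample taken at the early pregnancy visit before capsules start.
- **Weight gain.** Define it from the weight at the early pregnancy visit, and name the 34 week weight as the end point. Analyse 34 week weight by linear regression on allocation, first weight and gestational age at both weighings, in place of a t test on raw gain.

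The cost is corrected wording and a few covariates that the scheduled visits can supply. One small caveat is that gestational age at the last weighing is measured after randomisation, so the result without that covariate should be shown beside it.

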**Discussion:**

This trial is evaluating two approaches to improving maternal diet: a behaviour change intervention and vitamin D supplementation. The factorial design of this trial has the advantage of enabling each intervention to be tested separately as well as allowing exploration of the synergistic effect of both interventions on women’s diets and vitamin D levels.

**Trial registration:**

ISRCTN07227232. Registered on 13 September 2013.

## Background

The nutritional status and health of mothers influence the growth and development of infants during pregnancy and postnatal life [1]. Growth and development at these stages of the lifecourse will influence the risk of non-communicable diseases such as cardiovascular disease and obesity in adulthood. Interventions that focus on improving the nutritional status and lifestyle of mothers have the potential to optimise the growth and development of the fetus as well as improve the health of mothers themselves. Studies have shown that maternal nutrition influences child body composition [2, 3]. There are two principal approaches to improving the nutritional status of pregnant women: nutritional supplementation (multiple-micronutrient supplementation as well as single vitamin supplements to correct deficiencies) or behaviour change interventions that aim to improve the diet quality of pregnant women [4]. Improving the diets of women of childbearing age is likely to require complex interventions that are delivered in a socially and culturally appropriate context [5].

Multiple-micronutrient approaches have improved maternal and birth outcomes in studies of pregnant women in developing countries [6]. In Mumbai, India, for example, a food-based multiple-micronutrient supplement started preconceptionally and given throughout pregnancy halved the prevalence of maternal gestational diabetes [7]. Correction of specific vitamin deficiencies during pregnancy has improved outcomes for pregnant women and their babies in developed and developing country settings [8]. In a recent UK multi-centre trial of vitamin D supplementation during pregnancy, the Maternal Vitamin D Osteoporosis Study (MAVIDOS), supplementation corrected maternal vitamin D deficiency and optimised infant levels of vitamin D [9, 10].

Behaviour change approaches during pregnancy have the potential to improve the health behaviours of pregnant women and, whereas nutrient supplementation addresses specific nutrient deficiencies, behaviour change approaches can improve overall diet quality. Most pregnant women want to do their best for their baby, and so pregnancy presents an opportunity to tackle unhealthy lifestyle choices, such as smoking, and to promote healthy ones, such as intention to breastfeed [11]. Women’s confidence or self-efficacy that they can make such changes is an important determinant of whether their health behaviours will improve [12]. Low levels of self-efficacy are a barrier to healthful eating among women from disadvantaged backgrounds [13], and many studies have demonstrated a relationship between higher levels of self-efficacy and better dietary behaviours [14]. Reviews of evidence have provided useful insights into the features of behaviour change interventions associated with effectiveness in women of childbearing age and disadvantaged groups: providing information on risks and benefits of health behaviours combined with goal setting and continued support after the initial intervention were more likely to lead to behaviour change [15, 16].

The evidence points to the need for empowerment approaches that work by improving the self-efficacy of participants. We applied such an approach to an intervention which aimed to improve the health behaviour of women from disadvantaged backgrounds, a group in which there is an established link between low self-efficacy and poor quality diet [13, 17]. The intervention, the Southampton Initiative for Health (SIH), aimed to improve the diets of women from disadvantaged backgrounds. The intervention involved training Sure Start Children’s Centre staff, who work with women and children from disadvantaged families, in skills to support behaviour change [18]. The training led to changes in the way the staff interacted with women and, one year after training, staff in the intervention area were still using these skills and were using them significantly more than staff in the control area [19]. Evaluation showed that the intervention had a protective effect on the sense of control and self-efficacy of women who came into contact with trained staff, intermediate factors on the causal pathway between exposure to the intervention and change in diet and physical activity, though an influence on diet was not observed [20]. These findings suggested that the intervention has the potential to improve health behaviours in settings that offer women greater and more frequent exposure to trained staff. Pregnancy and childbirth offer such a setting.

Evidence from two recent UK trials supports the potential of behaviour change interventions during pregnancy to improve the healthfulness of women’s diets. In the UPBEAT and LIMIT trials, women received regular support from health care workers throughout their pregnancies. In LIMIT, the intervention was informed by stage theories of health decision making and comprised advice on behavioural strategies for healthful eating and increased physical activity that was delivered by a research dietician and trained research assistants. Women were encouraged to set diet and exercise goals and to self-monitor their progress towards these goals [21]. In UPBEAT, the intervention was informed by social cognitive theory. Health trainers delivered eight weekly sessions in which women received advice on improving diet and physical activity through a range of strategies, including identification of barriers to change, setting of SMART goals and self-monitoring [22]. These behaviour change interventions led to improvements in diet, although they did not improve the primary outcomes of gestational diabetes and babies born large for gestational age [21, 22]. Importantly, both interventions adopted empowerment approaches, suggesting that such an approach is likely to be successful in bringing about behaviour change.

Given that both supplementation and behaviour change intervention approaches have led to improvements in the diets of pregnant women, it is possible that interventions that combine both approaches might have a greater impact on diet than when each is delivered on its own. Evidence of the importance of self-efficacy as a predictor of women’s diets indicates that interventions that are effective in improving maternal diet will need to take account of women’s social circumstances and the barriers to healthy eating that they experience in their daily lives. This suggests that complex multi-component interventions will be required to bring about the sort of changes in women’s diets that are important for the health of their babies and has led us to assess such a multi-component intervention using a factorial design.

In the Southampton PRegnancy Intervention for the Next Generation (SPRING) trial, we have combined a behaviour change approach with vitamin D supplementation. We believe that this approach to improving health behaviour through enhancement of women’s self-efficacy has the potential to address barriers to taking supplements during pregnancy as well as to improve overall dietary quality.

### Aims

There are three aims of this trial. The first is to assess the efficacy of a behaviour change intervention (Healthy Conversation Skills) in improving the diet quality of pregnant women. The second is to assess the efficacy of oral daily vitamin D supplementation in improving the vitamin D status of pregnant women. The third is to explore the efficacy of an intervention combining vitamin D supplementation and behaviour change support in improving the diet quality and nutritional status of pregnant women.

### Study design

The study is a randomised controlled trial that uses a two-by-two factorial design. The two interventions being tested are exposure to nurses trained in skills to support behaviour change (Healthy Conversation Skills) and daily oral vitamin D supplementation (1000 IU cholecalciferol daily). The women taking part in the study and the research nurses delivering the intervention are blind to the vitamin D intervention, so this part of the trial is double blind. However, the same is not possible for the behaviour change intervention. There are four groups of study participants:Healthy Conversation Skills support plus vitamin D supplementationHealthy Conversation Skills support plus placeboUsual care plus vitamin D supplementationUsual care plus placebo.

### Primary outcomes

Given the factorial design of the trial, there are two primary outcomes:Maternal circulating plasma 25(OH) vitamin D concentration at 34 weeksMaternal diet quality at 34 weeks gestation assessed with a 20-item food frequency questionnaire [23]

